### Secondary endpoint in-scaffold late lumen loss at 12-month:

A weighted mean of 0.33 mm for in-scaffold late lumen loss and a weighted pooled SD of 0.35 mm were calculated based on the 12 month results of below listed clinical trials.

| Scaffold          | In scaffold LLL (mm)
@ 12 months
Mean (SD)     | N        | Publication             |
|-------------------|------------------------------------------------------|----------|-------------------------|
| Absorb            | 0.27 (0.32)                                          | 56       | Serruys 2011 (38)       |
| Magmaris          | 0.39 (0.34)                                          | 99       | Haude 2018 (21)         |
| Fantom II         | 0.29 (0.36)                                          | 31       | Gomez Lara 2011 (124)   |
| Mirage Vs. Absorb | 0.37 (IQR: 0.08 to 0.72)
0.23 (IQR: 0.15 to 0.37) | 35
27 | Tenekecioglu 2017 (125) |

For the DREAMS 3G the in-scaffold late lumen loss is estimated to be 0.33 mm.

The null and alternative hypotheses for non-inferiority testing of the powered secondary are formulated as the following:

$$H_0: \mu_2 \geq \mu_{02} + \Delta$$

$$H_a: \mu_2 < \mu_{02} + \Delta$$

Here,  $\mu_2$  is the mean in-scaffold LLL of DREAMS 3G at 12 months after index procedure,  $\mu_{02}$  is the historical control value derived as the weighted mean of in-scaffold LLL at 12 months obtained from the literature review ( $\mu_{02} = 0.33 \text{ mm}$ ), and  $\Delta$  is the prespecified non-inferiority margin ( $\Delta = 0.145 \text{ mm}$ ).

Substituting the absolute values, the hypotheses can be simplified to the following:

$$H_0: \mu_2 \geq 0.475 \text{ mm}$$

$$H_a: \mu_2 < 0.475 \text{ mm}$$

The sample size calculation is made with:

|                               |       |
|-------------------------------|-------|
| Power:                        | 0.95  |
| Alpha:                        | 0.025 |
| NIM (Non-Inferiority Margin): | 0.145 |
| S (Standard Deviation):       | 0.35  |
| Dropout rate:                 | 25%   |

Rejection of the null hypothesis will mean that in-scaffold LLL of DREAMS 3G is non inferior to the historical control at 12-month. A total of 104 subjects enrolled (78 subjects plus 25% dropout) will have 95% power to reject the above null hypothesis in favor of the alternative assumptions.

Conclusion: as the study is powered for both endpoints at 6 and 12-month, a total of up to 104 subjects need to be enrolled in order to prove non-inferiority of the DREAMS 3G scaffold vs. historical control devices. Increasing the number of enrolled subjects beyond the sample size requirement of evaluable subjects, in order to account for potential losses to follow-up will result in a total number of up to 115 patients to be enrolled.

Sample size was calculated using PASS 15 and planning for a one sample t-test.

### 7.3 Analysis Methods

Descriptive statistics will be presented for all baseline, procedure and FUP data, as well as device and procedure success, and angiographic endpoints.

For quantitative variables, the mean values, standard deviation, median, maximum and minimum, as well as the 95% CI (confidence interval) for the mean will be calculated. For qualitative variables, absolute and relative frequencies are determined, and the exact 95% confidence interval for proportions is calculated when relevant.

Adverse event rates will refer to the respective time intervals (e.g. 365 +/- 30 days).

Hypothesis testing will be performed for the primary endpoint using one sample one-sided non-inferiority t-test, see section 7.2.

For all clinical secondary endpoints and their components (TLF, cardiac death, all-cause mortality, TV MI, CD TLR, CD TVR, Definite and probable scaffold thrombosis) the survival rate (and 95% CI) will be calculated using Kaplan-Meier estimator. Kaplan-Meier survival curves will also be presented.

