### 1-Primary endpoint in-scaffold late lumen loss at 6-month:

A weighted mean of 0.29mm for in-scaffold late lumen loss and a weighted pooled SD of 0.34mm were calculated based on below 6-month data from listed clinical trials.

|                  | In-scaffold LLL (mm)
@ 6 months
Mean (SD) | N | Publication   |
|------------------|----------------------------------------------------------|----------|----------------------|
| ABSORB    | 0.44(0.35)                                               | 26       | Ormiston 2008 (46)   |
| ABSORB    | 0.19(0.18)                                               | 41       | Serruys 2010 (37)    |
| Desolve   | 0.19(0.19)                                               | 14       | Verheye 2014 (94)    |
| Magmaris  | 0.44(0.36)                                               | 113      | Haude 2016 (11)      |
| Desolve   | 0.20(0.32)                                               | 113      | Abizaid 2016 (70)    |
| Fantom II | 0.25(0.4)                                                | 100      | Chevalier 2019 (102) |

For the DREAMS 3G the in-scaffold late lumen loss is thus estimated to be 0.29 mm.

The null and alternative hypotheses for non-inferiority testing of the primary endpoint are formulated as the following:

$$H_0: \mu_1 \geq \mu_{01} + \Delta$$

$$H_a: \mu_1 < \mu_{01} + \Delta$$

Here,  $\mu_1$  is the mean in-scaffold LLL of DREAMS 3G at 6 months after index procedure,  $\mu_{01}$  is the historical control value derived as the weighted mean of in-scaffold LLL at 6

months obtained from the literature review ( $\mu_{01} = 0.29 \text{ mm}$ ), and  $\Delta$  is the prespecified non-inferiority margin ( $\Delta = 0.145 \text{ mm}$ ).

Substituting the absolute values, the hypotheses can be simplified to the following:

$$H_0: \mu_1 \geq 0.435 \text{ mm}$$

$$H_a: \mu_1 < 0.435 \text{ mm}$$

The sample size calculation is made with:

|                               |       |
|-------------------------------|-------|
| Power:                        | 0.95  |
| Alpha:                        | 0.025 |
| NIM (Non-Inferiority Margin): | 0.145 |
| S (Standard Deviation):       | 0.34  |
| Dropout rate:                 | 15%   |

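### Section 7.2 sizes the trial on a formal 12-month non-inferiority test that section 7.3 does not list, and the protocol does not order it against the 6-month test

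*Protocol*

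**What the plan says.** Section 7.2 contains two complete sample size calculations. The 6-month one, for the primary endpoint, uses a null of 0.435 mm or more, alpha 0.025, power 0.95, SD 0.34 mm and 15% dropout. It arrives at 74 evaluable and 88 enrolled subjects.

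The 12-month one is introduced with "The null and alternative hypotheses for non-inferiority testing of the powered secondary are formulated as the following". It uses a null of 0.475 mm or more, the same margin of 0.145 mm, alpha 0.025 again, power 0.95, SD 0.35 mm and 25% dropout. It arrives at 78 evaluable and 104 enrolled, and says that this number "will have 95% power to reject the above null hypothesis in favor of the alternative assumptions". It also states what rejection would mean, namely non-inferiority at 12 months.

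The conclusion of 7.2 takes the larger number, "as the study is powered for both endpoints at 6 and 12-month", and adds a reserve up to 115. It closes with "Sample size was calculated using PASS 15 and planning for a one sample t-test".

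Section 7.3 says of inference: "Hypothesis testing will be performed for the primary endpoint using one sample one-sided non-inferiority t-test". That sentence ends with a reference back to 7.2. The opening sentence of 7.3 places angiographic endpoints among the data to be described. Section 4.2 states a hypothesis for 6 months only. Section 7.5 schedules a 12-month analysis after the 6-month one and does not make it depend on the 6-month result.

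**The concern.** Sections 7.2 and 7.3 disagree on whether a confirmatory 12-month test exists. If 7.3 is taken as written, the test that set the enrolment is never run. The required number then exceeds the primary endpoint's need by 104 − 88 = 16 subjects, each given a first-in-man device and scheduled for invasive imaging at 6 and 12 months.

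If 7.2 governs, there are two confirmatory tests, each at the full one-sided 0.025. Nothing splits the alpha, sets an order or requires both to succeed. A 12-month non-inferiority claim would then remain open after a failed 6-month test, and the chance of at least one false claim across the pair would exceed 2.5%.

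**Working it through.** **Step 1. Reproduce the plan's figures.** Exact one-sample, one-sided t-test (noncentral t), shift equal to the margin of 0.145 mm, true difference from control 0 (section 7.2 expects 0.29 mm at 6 months and 0.33 mm at 12 months, the control values), alpha 0.025, target power 0.95. Enrolment = evaluable / (1 − dropout).

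| | SD (mm) | Evaluable | Power | Enrolled |
|---|---|---|---|---|
| 6 months | 0.34 | 74 | 0.952 | 74 / 0.85 = 87.06, so 88 |
| 12 months | 0.35 | 78 | 0.951 | 78 / 0.75 = 104 |

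All four figures match section 7.2. At one-sided 0.05 the evaluable numbers would be 61 and 65, so each calculation did use the full 0.025.

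**Step 2. Chance of at least one false claim, if both tests run with no order.** With both nulls true at their boundary and normal test statistics of correlation ρ:

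error = 1 − P(Z₁ ≤ 1.96, Z₂ ≤ 1.96)

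| ρ | 0 | 0.3 | 0.5 | 0.7 | 0.9 | 0.95 |
|---|---|---|---|---|---|---|
| Error | 4.94% | 4.76% | 4.54% | 4.17% | 3.52% | 3.23% |

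At ρ = 0 this is 1 − 0.975² = 4.94%. The Bonferroni bound is 5.0%.

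**Step 3. A plausible ρ.** The protocol gives none for the new device. Section 1.1.3 (BIOSOLVE-II) reports paired in-scaffold loss in 42 patients of 0.37 mm and 0.39 mm at 6 and 12 months, P = 0.446. Assume a two-sided paired t-test:

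- t on 41 degrees of freedom = 0.770, so the standard error is 0.02 / 0.770 = 0.026 mm.
- SD of the difference = 0.026 × √42 ≈ 0.168 mm.
- ρ = (s₁² + s₂² − 0.168²) / (2 s₁ s₂). With SDs between 0.34 and 0.36 mm (the predecessor's 12- and 6-month values in section 7.2), ρ is 0.88 to 0.89.

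At ρ = 0.88 the error is 3.6%. The two means are rounded, so their difference could lie between 0.01 and 0.03 mm. That gives ρ from 0.97 down to 0.72 and an error from 3.0% to 4.1%. If only 78 of 88 subjects contribute at 12 months, the correlation of the test statistics falls to 0.88 × √(78/88) = 0.83 and the error is about 3.8%.

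**Step 4. Effect of ordering the tests.** If 12 months is tested only after success at 6 months, the familywise error is 2.5% and the evaluable numbers stay as they are. The power to reach the 12-month claim is at least the sum of the two powers minus 1:

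- 104 enrolled (88 evaluable at 6 months, 78 at 12): 0.977 + 0.951 − 1 = 0.928.
- 115 enrolled (97 and 86 evaluable): 0.986 + 0.967 − 1 = 0.953.

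A Bonferroni split at 0.0125 each would need 91 evaluable at 12 months, or 91 / 0.75 = 121.3, so 122 enrolled. That is above the cap of 115.

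**The case against.** The sentence in 7.3 refers to 7.2, where both hypotheses stand, and it does not say that only the primary endpoint is tested. It may simply be an incomplete summary. That is a fair reading, but the same section assigns angiographic endpoints to descriptive statistics and section 4.2 has no 12-month hypothesis. The text has to be corrected under either reading.

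Chapter 7 calls itself an overview and leaves the final description to a SAP, and a testing order for a secondary endpoint is often fixed there. This stands as regards the missing order taken alone. It does not settle a disagreement between two sections of the protocol about whether the test exists.

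The labels primary and secondary, and the later date of the 12-month analysis, suggest that a 12-month result was not meant to rescue a failed 6-month one. They suggest it without stating it.

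A reader might also infer that the trial carries nearly double its stated error, or that CE approval may rest on either time point. The documents support neither. The inflation disappears if 7.3 is followed literally, or if both tests must succeed, which the wording in 7.2 about powering both endpoints allows. Values close to 5% need a low correlation, whereas the predecessor data point to a high one. The objectives tie CE approval to safety and clinical performance and contain no either-endpoint rule.

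**Conclusion.** The inconsistency is real and lies within the protocol: 7.2 sets up, powers and enrols for a confirmatory 12-month test that 7.3 does not list, and no text orders it against the 6-month test. It should be corrected before the 6-month result is known.

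The error-rate consequence is conditional and moderate. It arises only if 7.2 governs and a 12-month claim is allowed after a failed 6-month test. The chance of at least one false claim is then about 3.2% to 4.9% for correlations from 0.95 to 0, with about 3.6% the best-supported value. That value assumes that the predecessor's P value came from a paired t-test, that the SDs of larger samples apply to the 42 paired patients, and that the new device behaves similarly. The error of each single claim, the primary included, is 2.5% throughout.

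**What to change.** Add one sentence to section 7.3: in-scaffold late lumen loss at 12 months is tested against 0.475 mm with the same one-sample one-sided t-test at 0.025, only if the 6-month null hypothesis is rejected; otherwise it is reported descriptively. Exempt this endpoint from the descriptive listing in 7.3, and mention it in 4.2 so that the sections agree.

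Familywise error is then 2.5%. The sample size and the power of the primary test do not change. The cost is small: no formal 12-month claim is possible after a 6-month failure, and the power to reach that claim is slightly below the stated 95% at 104 enrolled (at least about 93%), returning to at least about 95% at 115.

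If no confirmatory 12-month claim is wanted, the alternative is to remove the 12-month hypothesis from 7.2 and justify enrolment above 88 on other grounds.

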#### **7.4 Missing Data**

All possible steps will be taken to minimize missing data in the study, including monitoring of data forms for completeness and efforts to track and maintain contact with study subjects during the follow-up period.

Unless otherwise noted, denominators for computation of percentages exclude subjects with missing data.

#### **7.5 Interim Analysis and Final Report**

An interim analysis is planned after all subjects have reached the primary endpoint at 6 months. Another analysis will be performed after all subjects have reached the 12 months follow up visit. Afterwards, annual interim reports will be issued upon request. The final report will be issued after 3 years follow up.

#### **7.6 Subgroup analysis**

Subgroup analyses may be performed ad hoc for exploratory purposes.

### **8. QUALITY CONTROL AND QUALITY ASSURANCE**

#### **8.1 Data Monitoring Committee**

##### **8.1.1. Data Safety Monitoring Board**

An independent Data Safety Monitoring Board (DSMB) will have the responsibility to assess in intervals, the progress of the clinical investigation, the safety data or the critical performance endpoints and to recommend the sponsor, whether to continue, suspend, modify or stop the clinical investigation.

Its conduct will be governed by a written DSMB charter describing its rules of operation and responsibilities.

### **8.1.2. Clinical Events Committee**

BIOTRONIK will instruct the centres to compile blinded source documents with the necessary data for the Clinical Events Committee (CEC). The CEC will meet depending on the event rate to review and adjudicate AEs, ADEs, SAEs, SADEs and USADEs. The decision of the committee is based on independent physician review of the eCRF and supporting source documentation, as required. All events will be supported by clinical data from the subjects' medical records. Classification of cause and circumstances surrounding the event will occur upon agreement of the reviewers. The classification system used and procedures implemented will be summarized in a CEC charter which will document the definitions and adjudication procedure.

Final adjudication of events will be done by the CEC. The adjudication by the CEC will overrule the one of the investigator, should the investigator and CEC disagree.

### **8.2 Core Laboratory**

A core laboratory (MedStar Health Research Institute, Maryland, USA) will be used for the independent assessment of image findings (angiographies, IVUS and OCT). Standard measurement process will be designed by the independent core laboratory and specified in written core laboratory guidelines. Each of the selected investigative sites will receive training on the acquisition, interpretation and transmission of images.

The images should be stored and sent according to core laboratory guidelines.

Any additional (unscheduled) imaging data should be collected and sent to the core laboratory as well.

### **8.3 Data Collection / Data MonitoringData Collection**

The investigator or an individual designated by the investigator is responsible for recording all data from the study in the electronic Case Report Form (eCRF).

The data will be entered in an electronic data capture system (EDC), compliant with the General Data Protection Regulation. Data should be entered within 5 days of the visit

and have to be done in English. Sites with incomplete or outstanding eCRFs may be prohibited from enrolment until data entry is complete.

All site staff must be trained on correct completion of the eCRF, before they are given access for data entry. All CRF pages must be electronically signed by the investigator or a person designated by the investigator at each site.

Subjects will only be identified in the eCRFs by a unique reference number, a composition of letters and numbers. eCRFs are confidential documents and will only be available to BIOTRONIK (including BIOTRONIK designees), the investigator, the clinical investigation statistician, and the DMC and regulatory authorities. The investigator or a person designated by the investigator will maintain as part of the clinical investigation file a subject's identification log of the subjects participating in the clinical investigation at the clinical investigation site.

An appropriate internet access is required for data entry and upload of pseudo-anonymised source documents.

### **8.3.2 Monitoring**

Monitoring will be performed by BIOTRONIK or by BIOTRONIK designees, to ensure that the investigator and the clinical investigation team conduct the clinical investigation in accordance with the CIP, current versions of Declaration of Helsinki, ISO 14155, International conference of harmonization-Good clinical practice (ICH-GCP) and applicable regulations to ensure adequate protection of the rights, safety and wellbeing of subjects and the quality and integrity of the resulting data.

Periodic monitoring visits will assure that the facilities are still acceptable; that the CIP is being followed, that the IEC/IRB has been informed about approved CIP changes as required, that records on study conduct and data collection are complete and present, that appropriate and timely reports have been made to the sponsor and the authorities, that device inventory is controlled, and that the investigator is carrying out all agreed activities.

During monitoring visits, 100 % source data verification as defined in the monitoring plan will be performed. For this purpose, the investigator must permit access to medical records of the subjects (source data) throughout the study. In case of

electronic medical records the investigator has to ensure that the monitor receives appropriate access or print outs of all study relevant source documents will be made (signed and dated by the investigator or other designated staff).

If a monitor becomes aware that an investigator is not complying with the requirements as outlined in the CIP, the monitor is obliged to notify BIOTRONIK study management. BIOTRONIK will evaluate the non-compliance and issue corrective actions, discontinue enrollment or as a last measure close the clinical investigation site. The investigator must in such case return all unused devices to BIOTRONIK.

#### **8.4 Source Data**

Original or signed and dated copies of all clinical findings, observations, and other activities throughout the clinical investigation must be recorded and maintained in the medical file of each enrolled subject. For data documented in the eCRF respective source data in the medical record (source document) must be available.

The medical record/subjects record (source document) must contain, but is not limited to:

- Executed informed consent
- Subjects participation in the clinical investigation
- Demographics
- Documentation of medical history
- Intervention report
- Vessel and lesion sizes and characteristics
- All angiographies, ECGs, laboratory examination outcomes including reference values
- Discharge letter
- All adverse events: diagnosis, symptoms, onset date, severity, device and procedure relationship, action taken, outcome
- Device deficiencies: including the assessment by the investigator whether the device deficiency is in connection with a malfunction, use error, inadequate labelling and whether the device deficiency is considered serious. Concomitant medication

- Follow-up information
- Date of clinical investigation completion

## 8.5 Data Management

The data manager is responsible for setting up an EDC system, its validation and maintenance during study duration. Queries (manual or pre-defined checks) are set up in the EDC system and should be resolved by the investigator or a person designated by the investigator in a timely manner. The data manager provides a clean data set at the end of the clinical investigation. Data snapshots will be performed for interim analysis. When all data is complete, the database will be locked and data analyzed.

## 8.6 Protocol Compliance

The investigator is required to conduct the study in accordance with the signed study agreement and clinical protocol.

The investigator shall notify BIOTRONIK and the reviewing IRB/IEC in writing, no later than 2 days after any significant violations from the study plan, conducted to protect the life or physical well-being of a subject in an emergency. Except in such emergency, prior approval by BIOTRONIK and, if applicable, IRB/IEC approval is required for significant violations from the study plan. Such an approval will be documented in writing and maintained in the study files.

BIOTRONIK categorizes instances of protocol non-compliance as either violations or deviations.

### 8.6.1 Protocol Violations

Protocol violations are defined as instances where the protocol requirements and/or regulatory guidelines were not followed and are generally more serious in nature. Protocol violations are considered to potentially affect the scientific soundness of the study and/or the rights, safety or welfare of subjects.

Protocol violations include, but are not limited to:

- Failure to obtain informed consent

- An unapproved (BIOTRONIK and IRB/IEC) investigator implanting an investigational device for study purposes
- Violation of relevant inclusion/exclusion criteria
- Protocol requirement violations that affect the primary endpoints analysis

In some instances, compliance issues with the consent process may occur. The investigator should seek guidance from the site's IRB/IEC to ensure the subject received appropriate information to consider their participation in the study. The investigator is obliged to take any action the IRB/IEC feels is necessary, including subjects removal from the study. Please note that subjects who haven't signed informed consent prior to implantation will not be included in the study analysis, even if informed consent could be obtained retrospectively.

All violations will be reported to the competent authority in accordance with applicable regulatory timelines. The study site should report the protocol violation to the reviewing IRB/IEC as applicable and provide a copy of the notification to BIOTRONIK. The site should also report the protocol violation to BIOTRONIK on the applicable CRF.

